#### Main Intervention: mPareshan Digital App

The mPareshan app has been designed based on feedback received from stakeholders in the formative phase. The app has 3 segments—tracking, counseling, and referral. The tracking segment records information on participant recruitment or retention and consent, and has interfaces for LHS, LHW, and study coordinator to access and record their feedback. Based on a 2-week recall, the referral segment identifies danger signs related to suicidal ideation, self-harm, and harm to others and then suggests appropriate referrals to the nearest mental health facility accordingly. In the absence of danger signs, the LHW is guided to the counseling segment of the app to deliver counseling to the SPs. This segment of the app has features of psychoeducation delivered through audio and video clips, breathing exercises, and imparts skills to cope with stress. The counseling segment has different content for each of the 6 sessions, which last around 20 minutes. An outline of the content covered in the 6 sessions is provided in Figure 2.

Prior to the commencement of the 20-minute counseling session, the LHW requests the SP to be seated in a comfortable, preferably less crowded place in the home. At the end of each session, the participant is instructed to practice breathing exercises as homework until the next session. The LHW ensures that the participant feels comfortable and consents to receiving the counseling. If the SP feels uncomfortable at any point in time, the session is discontinued.

Completion of counseling segment redirects the LHW to the section on feedback where she checks all activities that are performed in the session and records her written comments. Once submitted to the server by the LHW, the session gets locked and is passed on to her LHS for review. The LHS logs in from her portal to review all the feedback provided by the LHW and submits it to the study coordinator for a final check. The subsequent session gets unlocked for the LHW after 15 days of completion of the previous session.

These sessions coincide with LHWs’ scheduled monthly HH visits in their catchment area. The health workers assigned to the HH of SPs are trained to use configured Samsung Galaxy Tab A7 (4G; Samsung Electronics) on which the mPareshan app is downloaded. The training facilitators demonstrate how health workers are to operate tracking, referral, counseling, and feedback segments of the mobile app.

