### Sample Size Calculations

For the baseline screening survey, the sample size is calculated using OpenEpi (version 3.01; Emory University) [38]. Assuming a 30% prevalence of depression and anxiety symptoms among adults, at a 5% level of significance and 80% power, 323 people are required to assess point prevalence of depression and anxiety [39]. Catering to 10% refusals, the final sample size is 366 individuals.

For the change in mental health literacy of CHWs, a total of 72 LHSs and LHWs are required to detect a mean difference of 1.5 (SD 3.9) in pre- and posttraining knowledge and skills scores, assuming 5% significance level and 80% study power [40].

For receiving mPareshan app-based intervention, the sample size for recruitment of SPs is calculated using Medcalculator (version 19.8; MedCalc Software). Assuming a mean difference between pre- and postintervention of PHQ-9 scores of 1.5 (SD 5.6; mean score at baseline=11.61 and postintervention=10.1), the minimum sample size required at a 5% level of significance and 80% power is 112. Considering a 10% attrition rate, with some oversampling, the expected sample size is 123 for recruiting participants for the mPareshan intervention and demonstrating a reduction in symptoms [41].

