### Data Analysis

Baseline and end line data collected from respondents is being exported from REDCap to SPSS (version 21; IBM Corp). Frequency and proportion will be used to report categorical variables. Depending on the distribution of anxiety or depression scores of SPs and knowledge or skills scores of health workers, paired *t* tests or McNemar’s chi-square tests will be used to evaluate the change in outcomes. The mean difference with 95% CIs will be reported. A *P* value of <.05 will be considered statistically significant.

All interviews will be transcribed in English. Using NVivo (Lumivero), content analysis will be conducted on all IDI and FGD transcripts, and codes will be organized into either emergent or predetermined categories by the researchers. Commonalities and differences across the data will be identified and clustered around thematic sections. Verbatim quotes will be added to complement the themes. RE-AIM framework will be used to describe the feasibility outcomes [33].

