## Results

Data were collected in 2022-2023. At the time of this submission (April 2024), we are analyzing the results of 366 individuals who participated in the baseline prevalence survey, the change in knowledge and skills of 72 health workers who took the mPareshan training, change in anxiety and depression scores of 98 SPs recruited for app-based counseling intervention, and stakeholder perceptions gathered from 8 FGDs and 18 IDIs as part of qualitative assessments. Final data cleaning and data analysis are ongoing and the results will be disseminated through peer-reviewed publications in 2024.

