## Discussion

Project mPareshan will assess the feasibility of using frontline workers in early home-based screening of anxiety and depression, providing app-based mental health counseling and prompt referrals. The community will ultimately benefit as the mental well-being of the population improves by a projected decrease in mean symptomatic scores of anxiety and depression. The contextually adapted mhGAP training for health workers will also lead to an improvement in their mental health literacy thus building the capacity of the primary health care workforce in mental health service delivery.

Previous studies using mHealth modalities have used cellular devices for the purpose of making referrals and record-keeping [26]. Despite the high reported suicide rate, there is a lack of awareness about mental health and the availability of specialized mental health services is suboptimal in Badin District. The novel approach being tested in this trial is expected to improve the mental health of rural populations where access to health care is limited and difficult. Results from this study will be important in initiating a policy dialogue for horizontal integration of basic mental health counseling initiatives in the current primary health system of low-resource settings.

Implementation challenges in this trial in the field included partial disruption and delay in intervention execution attributed to natural disasters, for example, floods in 2022. Furthermore, fluctuations in internet connectivity partially compromised the delivery of the app-based counseling sessions initially. The current substantial workload of LHWs makes it difficult to add mental health counseling as part of their routine package of service delivery. Moreover, considering the small sample size of participants enrolled for receiving the intervention, the generalizability of study findings may be an issue.

Based on the anticipated results of this pilot project, mental health can be introduced as part of the LHW curriculum and service delivery package. This will set the stage for integrating mental health into primary health care.

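### The paired test and its 95% CI take screen-positive participants as independent, although some probably share a lady health worker; if change scores correlate within worker, precision is overstated, probably by a little

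*Protocol article*

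**What the plan says.** The Data Analysis section of the protocol article states that, depending on the distribution of the scores, paired t tests or McNemar "chi-square tests will be used to evaluate the change in outcomes". It adds: "The mean difference with 95% CIs will be reported". No term for LHW or catchment area is named.

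The Sample Size Calculations section assumes a mean change in "PHQ-9 scores of 1.5 (SD 5.6; mean score at baseline=11.61 and postintervention=10.1") and concludes that "the minimum sample size required at a 5% level of significance and 80% power is 112". It then says: "Considering a 10% attrition rate, with some oversampling, the expected sample size is 123". No design effect enters.

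On delivery, the section on the mPareshan app says: "The health workers assigned to the HH of SPs are trained" to use the app, and it ties the sessions to each LHW's monthly visits in her own catchment area. The Abstract and the Study Procedure Outline describe face-to-face, home-based sessions. The Results section reports that analysis is under way on the "change in anxiety and depression scores of 98 SPs recruited for app-based counseling intervention", and that 72 health workers took the training.

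**The concern.** SPs who have the same LHW receive the counseling through one person, with her skill and her adherence to the session content, and under one supervisor's review. They also live in the same area. The Discussion reports unstable internet connectivity and disruption from "natural disasters, for example, floods in 2022"; where these differed between areas, neighbors would share them too. Such influences act on the change between baseline and end line. Taking each person's difference therefore does not remove them, as it would remove a stable difference between areas.

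If change scores within an LHW are positively correlated, 98 SPs carry less information than 98 independent people. The standard error from a plain paired t test is then too small. What is at stake is the CI and P value for the study's clinical outcome. The estimate of mean change itself is not called into question.

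**Working it through.** **Inputs from the article.** Mean change 1.5, SD 5.6, 5% significance (taken as two-sided; sidedness is not stated), power 80%, minimum n 112 (Sample Size Calculations). SPs under analysis: 98; trained health workers, LHWs and lady health supervisors (LHSs) together: 72 (Results). LHSs in Badin: 36 (Study Site).

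**Assumptions.** ICC of the change scores within LHW: 0.05 to 0.10. Only trained workers deliver. The number of delivering LHWs, k, is not given and is varied below.

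**Step 1: the plan's own figure.** For a paired t test with difference 1.5 and SD of change 5.6 at two-sided 5%, the noncentral t distribution gives power 79.9% at n = 111 and 80.2% at n = 112. The stated 112 is reproduced exactly, and it is a figure for independent participants.

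**Step 2: planned precision at 98 SPs.** Standard error = 5.6/√98 = 0.566. The 95% half-width is 1.985 × 0.566 = 1.12 points. Power is 74.7%. This shortfall comes from having 98 rather than 112 SPs and has nothing to do with clustering.

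**Step 3: must SPs share a worker?** 98/72 = 1.36, so yes, if only trained workers delivered. The 72 is an upper bound on delivering LHWs: it includes LHSs, who review sessions, and it comes from the sample size for the literacy outcome. If all 72 came from Badin, at most 36 were LHSs, so at least 72 − 36 = 36 were trained LHWs. With 36 delivering, the mean is 98/36 = 2.72 SPs each.

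**Step 4: effect on the standard error.** Design effect DE = 1 + (m − 1) × ICC, with m = 98/k. The standard error and CI width are multiplied by √DE.

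| Workers k | m | ICC | DE | SE multiplier | 95% half-width |
|---|---|---|---|---|---|
| 72 | 1.36 | 0.05 | 1.018 | 1.009 | 1.13 |
| 72 | 1.36 | 0.10 | 1.036 | 1.018 | 1.14 |
| 36 | 2.72 | 0.05 | 1.086 | 1.042 | 1.17 |
| 36 | 2.72 | 0.10 | 1.172 | 1.083 | 1.22 |

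For the same rows, the actual type I error of a nominal 5% test, 2 × [1 − Φ(1.96/√DE)], is about 5.2%, 5.4%, 6.0% and 7.0%.

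**Step 5: uneven loads.** With coefficient of variation CV of SPs per LHW, DE = 1 + [(1 + CV²) × m − 1] × ICC. At an assumed CV of 1 and k = 72, DE = 1 + (2 × 1.36 − 1) × ICC, which is 1.086 at ICC 0.05 and 1.172 at ICC 0.10. These equal the values for 36 evenly loaded LHWs. At k = 36 and CV 1, DE is 1.22 to 1.44 and the standard error 11% to 20% larger.

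**The case against.** The strongest case against runs as follows. The article gives no ICC and no count of delivering LHWs. On the one worker count it does give, the adjustment is 1–2%, which would change no reading of a feasibility study. The app section suggests that those trained on the app are the workers assigned to SPs' households, which favors many deliverers with few SPs each. The floods and connectivity problems are described as general disruptions; a shock common to the whole district shifts the mean and creates no correlation within LHW. The scores sit in REDCap, collected by separate data collectors, while LHW submissions sit in the app; no linkage is described, and data are anonymized. With one or two SPs per LHW, a random intercept is poorly estimated. Finally, details of variance estimation are often left to an analysis plan, which is not shown.

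Much of this stands. The effect may be negligible, correlation is plausible rather than shown, and linkage takes some work. Two points do not carry. The article states the tests, so the method is not left open. And 72 is a ceiling on the number of delivering LHWs, so 1–2% is the low end for any given ICC.

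Some stronger readings are tempting but unsupported. A reader might infer group counseling; the sessions are individual and at home. A reader might take 20–25 as the number of delivering LHWs; in the Background that figure is the number of LHWs each LHS oversees. And the 75% power at 98 SPs should not be put down to clustering.

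**Conclusion.** The point holds in a limited form. The stated tests and CI ignore a plausible correlation among SPs of the same LHW, and some sharing is unavoidable if only trained workers delivered. At an assumed ICC of 0.05 to 0.10, the standard error would be about 1–2% larger with SPs spread evenly over 72 workers and about 4–8% larger with 36 delivering LHWs. It would be larger again with fewer LHWs or uneven loads. The lower bound of 36 trained LHWs rests on all 72 trainees coming from Badin, and nothing guarantees that all trained LHWs delivered.

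It would go too far to say that the CI will certainly be too narrow. That requires a positive ICC, which the article neither reports nor rules out. This is a worthwhile improvement to the analysis, not a flaw that undermines the study.

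**What to change.** Keep the mean paired change in PHQ-9 and in GAD-7 as the estimate. Compute its 95% CI and P value with cluster-robust standard errors by LHW, with a small-sample correction; a mixed model with a random LHW intercept is an alternative. Report the number of delivering LHWs, the distribution of SPs per LHW and the estimated ICC, and show the plain paired t test alongside. If McNemar's test is used on categories, give it the same treatment by LHW.

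The Results section says that analysis was still ongoing, so a sentence in the analysis text is enough. The cost is a slightly wider CI if the ICC is positive, and the work of linking the app's LHW identifier to the REDCap scores. In return, readers can see whether clustering matters here, and the variation between delivering workers is informative in itself for an implementation study.

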### Ethical Considerations

This study protocol has been approved by the Ethical Review Committee of Aga Khan University (ERC# 2021-6570-20015). mPareshan is an implementation research feasibility trial and is not a clinical or drug trial. No adverse events are, therefore, anticipated. Any participants exhibiting (the a priori–defined) danger signs will be immediately referred during participant recruitment or counseling phases. Written, informed consent is obtained from each participant in their local language at each phase of the study. Data are anonymized and participant confidentiality is maintained. No compensation is offered to SPs for participation in the counseling sessions.

## Results

Data were collected in 2022-2023. At the time of this submission (April 2024), we are analyzing the results of 366 individuals who participated in the baseline prevalence survey, the change in knowledge and skills of 72 health workers who took the mPareshan training, change in anxiety and depression scores of 98 SPs recruited for app-based counseling intervention, and stakeholder perceptions gathered from 8 FGDs and 18 IDIs as part of qualitative assessments. Final data cleaning and data analysis are ongoing and the results will be disseminated through peer-reviewed publications in 2024.

## Discussion

Project mPareshan will assess the feasibility of using frontline workers in early home-based screening of anxiety and depression, providing app-based mental health counseling and prompt referrals. The community will ultimately benefit as the mental well-being of the population improves by a projected decrease in mean symptomatic scores of anxiety and depression. The contextually adapted mhGAP training for health workers will also lead to an improvement in their mental health literacy thus building the capacity of the primary health care workforce in mental health service delivery.

Previous studies using mHealth modalities have used cellular devices for the purpose of making referrals and record-keeping [26]. Despite the high reported suicide rate, there is a lack of awareness about mental health and the availability of specialized mental health services is suboptimal in Badin District. The novel approach being tested in this trial is expected to improve the mental health of rural populations where access to health care is limited and difficult. Results from this study will be important in initiating a policy dialogue for horizontal integration of basic mental health counseling initiatives in the current primary health system of low-resource settings.

Implementation challenges in this trial in the field included partial disruption and delay in intervention execution attributed to natural disasters, for example, floods in 2022. Furthermore, fluctuations in internet connectivity partially compromised the delivery of the app-based counseling sessions initially. The current substantial workload of LHWs makes it difficult to add mental health counseling as part of their routine package of service delivery. Moreover, considering the small sample size of participants enrolled for receiving the intervention, the generalizability of study findings may be an issue.

Based on the anticipated results of this pilot project, mental health can be introduced as part of the LHW curriculum and service delivery package. This will set the stage for integrating mental health into primary health care.

## Appendix

Multimedia Appendix 1 Guide for focus group discussions and in-depth interviews used for qualitative assessments to assess feasibility and uptake of intervention.

## Abbreviations

CHW: community health worker
CP: community participant
FGD: focus group discussion
GAD-7: Generalized Anxiety Disorder-7 Scale
HH: household
IDI: in-depth interview
LHS: lady health supervisor
LHW: lady health worker
LHW-P: Lady Health Worker Programme
LMIC: low- and-middle income country
mHealth: mobile health
mhGAP: Mental Health Gap Action Programme
mhGAP-IG 2.0: Mental Health Gap Action Program-Intervention Guide V2.0
PHQ-9: Patient Health Questionnaire-9
REDCap: Research Electronic Data Capture
RE-AIM: reach, effectiveness, adoption, implementation, and maintenance
SP: screen positive
WHO: World Health Organization
